**Study Assessments**	**Screening**	**Transfusion Support Periods** • **Day 1 through Day 28 *****and*** • **28-Day plus 6-month extension (or death-up to 10 transfusion episodes)**		**Follow-Up Visit Day 28* (28 ± 7 days) after last study transfusion episode**	**End of Study-Day 75 of** ** Follow-Up (75 ± 15 days) after last study transfusion**
		**Before each transfusion episode**	**15 min—24 h. after each transfusion episode**		
Informed Consent (assent, if appropriate)	X^1^				
Medical, surgical, prior transfusion and medication history	X^1^				
Physical exam, including height	X^1^				
Weight	X^1^				
Demographics	X^1^				
ABO Blood type and Rh^3^	X^1^	X^3^			
Indirect Antiglobulin Test^3^	X^1^	X^3^		X	
DAT^8^	X^1^			X	X
Immune reactivity to amustaline/GSH RBCs (amustaline/GSH RBC antibody testing)	X^1^	X^7^		X	X
Pregnancy test (if applicable)^3^	X				
Indication for RBC transfusion	X^1^				
Hematology panel^9^	X^1^	X		X	
Hemoglobin measurement			X^2^		
Blood chemistry panel^10^	X^1^	X		X	
Coagulation panel^11^	X^1^			X	
Vital signs	X^1^	X	X	X	
RBC transfusion data (study or non-study)	X^1^	X		X^5^	
Concomitant medications	X^1^	X^4^		X	
Other blood components transfused		X		X	
Procedure details (as applicable, e.g., surgery)		X			
Adverse events and transfusion reactions		X	X	X^13^	
SAEs		X	X	X^13^	
Surveillance calls ^12^		X		X	
Documentation of vital status		X		X	X
Assess proportion of each RBC component transfused (e.g., 25%, 50%, 75% or 100%) For pediatric patients, the volume of the intended transfusion should be recorded			X		
Assessment of bleeding status^6^	X	X			

‡ Randomization of eligible subjects may occur any time up to 30 days prior to first study transfusion

* Day 1 of the follow-up period is the first day after the last study transfusion

^1^If results from the Screening assessments listed are available in the medical record within 30 days prior to randomization, those data may serve as the screening data and the assessments do not need to be repeated unless the subject has an RBC transfusion in the 30-day period. If an RBC transfusion occurs after determined eligibility but prior to randomization, the subject may be randomized, and those Screening assessments listed above should be repeated prior to the first study transfusion

^2^Hb measurement at 15 min to 24 h post transfusion episode (before the next RBC transfusion episode)

^3^Routine standard of care test order per local hospital SOPs

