### 28-day (± 7 days) post-transfusion support follow-up period

Day 1 of the 28-day (± 7 days) follow-up period is the first day after the last study transfusion. The last study transfusion will occur no later than the end of the 28-day acute transfusion period or the 6-month extension period. For subjects enrolled in the 6-month extension period, the last study transfusion may also be the tenth transfusion episode for repeated simple transfusion subjects, or the third RCE episode in SCD subjects. At least one monthly surveillance call will be performed with all subjects to collect data on AEs, SAEs, TRs and UADEs during the 28-day (± 7 days) follow-up period. On Day 28 (± *7* days) after the last study transfusion, subjects will return to the study site for the following assessments: Vital signs, AEs, SAEs, TRs, comorbid conditions, blood samples for safety labs (hematology, blood chemistry, and coagulation panels), IAT and DAT, and immune reactivity to amustaline/GSH RBCs. Samples may be used for additional in vitro research testing as required to confirm transfusion-transmitted pathogen mediated infections.

For SCD patients undergoing regular RCE, the assessments described in Table 4 should be collected on Day 28 (± *7* days).

**Table 4 Tab4:** Laboratory Assessments for SCD Subjects Enrolled in the RCE Arm

• Hematology panel• Reticulocytes • Proportion (%) of HbS, HbA, and HbF • Coagulation panel • Plasma frozen sample for determination of S-300 and GSH concentrations	

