Non-study RBCs received during the study transfusion period will be included in the calculation of Hb content transfused. For each non-study RBC component received, the Hb content will be imputed using the average Hb content per study RBC component from the Control group within each clinical site.

The treatment difference in the adjusted Hb increment will also be summarized descriptively (with a 95% confidence interval) as exploratory analyses for the following mITT subgroups:Repeatedly transfused non-bleeding patients (defined as non-bleeding patients who receive at least 3 study RBC episodes).Subgroup by clinical site, age group (< 18, 18–64, and ≥ 65 years old), sex, and race (e.g., white vs. other races), as appropriate.

For SCD patients enrolled in the 6-month extension for three RCE procedures, HbA clearance will be estimated from the area under the curve (AUC) calculated by the trapezoidal rule based on measurements from samples collected within 4-h of each RCE, on Day 14 (± 7-days) and prior to the next scheduled RCE. Values will be adjusted by the duration in days used to calculate the AUC (i.e., between the 15 min-to-4-h post-transfusion sample and pre-transfusion sample of the next transfusion) and averaged over all study RCE procedures for each patient.

For the secondary efficacy endpoint of Hb consumption, the analysis will be conducted only in non-bleeding mITT patients who participate in both of the initial 28-day and 6-month extension periods and will utilize integrated data from both periods. Treatment differences in non-bleeding mITT patients will be assessed using the same non-inferiority test methods described above for the primary endpoint analysis. Interaction terms between the treatment and covariates will be explored, as necessary. For the adjusted Hb consumption analysis, the upper bound of a two-sided 95% confidence interval for the treatment difference (Test – 1.15 × Control) less than or equal to zero will result in the rejection of inferiority null hypothesis and the conclusion of non-inferiority.

Adjusted Hb consumption will be calculated as total Hb mass transfused in grams divided by body weight in kg at baseline and duration of the study transfusion period in days (g/kg/day). The total Hb mass transfused is the sum of the Hb content for all study and non-study RBC components transfused during the study transfusion period (i.e., 28 days or 28-day + 6-months, unless subjects prematurely discontinue the study).

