For patients who prematurely discontinue from the study, the duration of the study transfusion period will be calculated as:

$$\left(end\;date\;of\;study\;transfusion\;period\right)-\left(start\;date\;of\;first\;study\;RBC\;component\right){+1}$$

Where the end date of the study transfusion period will be defined according to the following rules:For subjects who withdraw due to death, the date of death will be the end date of the study transfusion period.For patients withdrawn for reasons other than death (e.g., lost to follow-up, withdrawal of consent, AE), the last date of a study or non-study RBC transfusion during the planned study transfusion period (28-days or 28-day + 6-months) will be the end date of the study transfusion period.

The treatment difference in the adjusted Hb consumption will also be summarized descriptively as exploratory analyses for the following mITT subgroups:Repeatedly transfused non-bleeding patients (defined as non-bleeding patients who receive at least 3 study RBC episodes).Subgroup by clinical site, age group (< 18, 18–64, and ≥ 65 years old), sex, and race, as appropriate.

Only mITT patients will be included in the safety analysis. Treatment-emergent AEs are defined as AEs with an onset date/time that is on or after the start date/time of the first study RBC transfusion. AEs will be summarized by treatment group, system organ class (SOC), and preferred term as applicable. The proportion of patients with AEs possibly, probably, or definitely related to study RBC transfusion will be compared between treatment groups using a Cochran-Mantel–Haenszel (CMH) test (controlling for clinical site and baseline bleeding status). The risk difference associated confidence interval will also be reported. In the event of sparse counts, Fisher’s exact test may also be used to provide statistical interpretation.

To investigate the potential impact of irradiation, subgroup analysis by irradiation status (yes vs. no) may be presented for the primary efficacy endpoint and selected safety data (including SAEs, AEs, and potassium level).

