This study design is associated with a number of potential limitations. In the absence of an acute epidemic or pandemic threat, enrollment and subject selection in transfusion medicine studies can be challenging due to competing trials and lack of patient awareness of transfusion medicine topics. Furthermore, the 6-month extension of this study has a significant on-study time commitment and potentially high number of study related activities (depending on the number of transfusions occurring during that period). Amendment 9 of the protocol limits the number of on-study transfusions to a maximum of ten. This change is designed to streamline recruitment in the 6-month extension arm and improve representativeness of the long-term cohorts as much as possible.

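### The duration rule for adjusted Hb consumption does not cover subjects who reach the ten-episode cap; read literally, it dilutes a Test-Control difference and favours non-inferiority

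*Protocol article*

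**What the plan says.** All references are to the protocol article.

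- **Endpoint (Statistical methods).** Total Hb mass is "divided by body weight in kg at baseline and duration of the study transfusion period in days (g/kg/day"). The mass is the "sum of the Hb content for all study and non-study RBC components transfused during the study transfusion period". Non-inferiority is concluded if the upper 95% confidence bound for Test − 1.15 × Control is at or below zero. The analysis set is non-bleeding mITT subjects who take part in both the initial period and the extension.
- **Length of the period (Statistical methods).** It is "i.e., 28 days or 28-day + 6-months, unless subjects prematurely discontinue the study". A shorter duration is given only under the sentence "For patients who prematurely discontinue from the study, the duration of the study transfusion period will be calculated as", with end dates for death and for other withdrawals.
- **Cap.** The Discussion says "Amendment 9 of the protocol limits the number of on-study transfusions to a maximum of ten". The section on the 28-day follow-up says that "the last study transfusion may also be the tenth transfusion episode for repeated simple transfusion subjects".
- **A different period (Table 1 header).** The support period is labelled "28-Day plus 6-month extension (or death-up to 10 transfusion episodes").
- **Non-study RBCs.** For each such component, "the Hb content will be imputed using the average Hb content per study RBC component from the Control group within each clinical site". Table 1 schedules RBC transfusion data up to the Day 28 follow-up visit and not at Day 75. Footnote 5, attached to the Day 28 cell, asks for dates of non-study transfusions in the 28-day follow-up and, if applicable, in the 6-month extension.

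**The concern.** If PR-RBCs were lost faster than conventional RBCs, Test subjects would need transfusion at shorter intervals. Hb consumption is the endpoint that would show this, and the extension was added to study repeated transfusion.

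A subject who reaches episode ten has completed study transfusion as planned, so the premature-discontinuation rule does not apply and the literal divisor remains 28 days + 6 months. After the cap, subjects in both arms can receive only conventional RBCs. That stretch therefore carries no information about the randomised product, yet it enters both parts of the ratio. If non-study units in that stretch are also missed, the divisor grows while the numerator does not, and the loss is larger in the arm that reaches the cap sooner. Both effects pull the recorded ratio toward 1, the direction that favours non-inferiority.

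**Working it through.** **Inputs.** Window D = 28 + 182 = 210 days (211 if six months is 183 days). Extension target 140, of whom up to 30 are RCE subjects, who count as bleeding: 140 − 30 = 110, about 55 per arm (Sample size). Transfusion intervals and the CV of Hb mass are assumptions. The only CV in the article is 50%, for the primary endpoint. The article gives no power figure for Hb consumption, so there is none to reproduce. Its primary-endpoint figure does reproduce: margin 15, SD 50 and one-sided 0.025 give 175 per arm (350 in total) by the normal approximation, and 176 per arm by the noncentral t, against the stated 352.

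**When the cap binds.** With the first episode on day 1 and interval d, episode ten falls on day 1 + 9d and episode eleven on day 1 + 10d. Within 211 days, episode ten needs d ≤ 210/9 = 23.3 and episode eleven needs d ≤ 210/10 = 21.

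**Episodes entering the numerator over 211 days**

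| Interval (days) | Day of episode 10 | Study RBCs only | Plus non-study RBCs to 28 days after episode 10 | All RBCs in window |
|---|---|---|---|---|
| 7 | 64 | 10 | 14 | 31 |
| 14 | 127 | 10 | 12 | 16 |
| 21 | 190 | 10 | 11 | 11 |
| 28 | not reached | 8 | 8 | 8 |

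**Capture.** For a weekly subject, the Day 28 visit is at 64 + 28 = day 92 and the end of study at 64 + 75 = day 139. About 210 − 139 = 71 days of the divisor then fall after the last scheduled contact. Surveillance calls run to 28 days after the final study transfusion and are listed for safety events. Day 75 schedules the DAT, the antibody test and vital status.

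**Inconsistency between the rules.** If that weekly subject withdraws just after episode ten, the divisor is 64 − 1 + 1 = 64 days, and the value is 10/64 = 0.156 episodes per day. If the subject completes, the value over 211 days is 31/211 = 0.147 with full capture, but 14/211 = 0.066 with capture to the Day 28 visit.

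**One worked pair at the margin.** Control every 14 days; Test every 14/1.15 = 12.17 days, with Test subjects assumed to return to 14 days on conventional RBCs after the cap.

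- Full capture: Test reaches episode ten on day 1 + 9 × 12.17 = 110.6, then adds (211 − 110.6)/14 = 7.2, total 17.2. Control has 16. Ratio 17.2/16 = 1.07.
- Capture to 28 days after episode ten: Test 10 + 2 = 12, Control 10 + 2 = 12. Ratio 1.00.
- Period ended at episode ten: (10/110.6)/(10/127) = 0.0904/0.0787 = 1.15.

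**Simulation.** 55 per arm, true ratio 1.15, interval distributions lying within 7-28 days, CV of Hb mass 25-50%, criterion on Test − 1.15 × Control, and the same return to the Control interval after the cap:

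| Rule for capped subjects | Recorded ratio | False non-inferiority (nominal 2.5%) |
|---|---|---|
| Full window, all post-cap units captured | 1.08-1.11 | 6-18% |
| Full window, capture to Day 28 visit | 1.00-1.06 | 13-81% |
| Period ended at episode ten | close to 1.15 | about 2-4% |

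In the two full-window rows, the low ends come from intervals of 14-28 days with CV 50% and the high ends from 10-21 days with CV 25%. For intervals of 21-35 days, where few subjects reach the cap, the error with follow-up units credited is about 4-5%.

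**The case against.** A reader might infer that frequently transfused subjects in both arms all score ten episodes over 210 days, so that non-inferiority is nearly automatic for them. The documents do not support this, for three reasons.

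- The numerator includes non-study RBCs, and footnote 5 asks for their dates in the extension. On the text as written, weekly, two-weekly and three-weekly subjects contribute 31, 16 and 11 episodes, not ten each.
- The endpoint is in g/kg/day, so grams per episode and body weight still vary even where episode counts agree.
- The test is on arm means. Suppose every post-cap unit were ignored and the recorded ratio were exactly 1. The standard error relative to the Control mean is CV × √((1 + 1.15²)/55). At CV 50% this is 0.103, and the chance of passing is Φ(0.15/0.103 − 1.96) = 0.31. At CV 30% it is 0.68. Neither is close to certainty.

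Two further points count against the concern. The Table 1 header permits a reading under which the period ends at episode ten and the bias disappears. The SAP, which is not shown here, may define the derivation. Also, if a shorter Test interval persisted after the switch to conventional RBCs and every unit were captured, the ratio would stay near 1.15 and the error near 3%.

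What stands is narrower. The article itself states a duration rule, that rule omits a planned end of study transfusion, and its own table suggests another end. Counting non-study RBCs reduces the dilution but does not remove it where the excess use is due to the Test product, because the post-cap units are conventional in both arms and imputed at the Control average. Footnote 5 asks for dates across the extension, but no scheduled contact covers the late part of the window for subjects who reach the cap early.

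**Conclusion.** The point holds as a gap and an internal conflict in the definition of a secondary endpoint. The stated rule leaves capped subjects on the full 28 days + 6 months, and the resulting dilution favours non-inferiority in subjects transfused at intervals under about 21-23 days.

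Its size depends mainly on how completely post-cap units are captured. The error at the margin is moderately inflated if every unit is captured and can be large if capture stops at the Day 28 visit. These figures rest on assumed intervals, an assumed CV, 55 per arm, and Test subjects reverting to a Control-like interval after the cap. The article does not say how many subjects will reach the cap. The effect is small when most intervals exceed about 23 days. The primary efficacy and safety endpoints are untouched.

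**What to change.** Before unblinding:

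1. Reconcile the Table 1 header and footnote 5, the follow-up section and the two duration statements in Statistical methods, so that one definition of the study transfusion period covers subjects who reach ten episodes. If the SAP already has such a rule, align the article with it.
2. For those subjects, end the consumption period at the tenth episode and take mass and days over that same period. Two workable forms are the Hb mass of episodes 1-9 over the days from the first episode to the start of the tenth, or all ten episodes to that date. Choose one and apply it alike in both arms.
3. Keep the full-window version, with all captured non-study RBCs, as a sensitivity analysis, and report how complete that capture is.

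**Cost.** One extra derivation from dates and masses already collected. Enrolment closed on 24 October 2025, the article describes the study as still blinded, and last assessments are expected in the third quarter of 2026, so there should be time. There is a small mismatch with uncapped subjects, whose fixed-window value counts the first episode. At 28 days, 8/210 = 0.0381 per day against 1/28 = 0.0357, about 7% high, whereas the nine-interval form gives the rate itself. With that form the error was 4-7% for intervals of 21-35 days, so the choice between the two forms should be checked against the intervals expected in this cohort.

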^4^Medications administered during anesthesia for surgical or other procedures are not collected

^5^The date of non-study RBC transfusion, if any, during the 28-day follow-up period and 6-month extension, if applicable, must be documented

^6^Daily for inpatients when available through the end of the acute transfusion period for inpatients

^7^Performed in conjunction with every routine standard of care test for ABO Type, Rh and screen (IAT) test that is performed during the Acute Support Period

^8^If, during the acute support period or follow up assessments (Day 28), a positive DAT result is observed, participating sites will follow their routine standard practice for confirmation/characterization of DAT positive samples; this should only apply to any conversion from a negative to a positive DAT after enrollment, that is not part of an investigation of hemolysis or of a positive IAT with evidence of an amustaline/GSH RBC antibody, in which case further investigations may be appropriate after discussion with the sponsor

^9^Hematology Panel: WBC, RBC, Hb, Hct, MCV, MCH, MCHC, MPV, RDW, PLT, Neutrophil %, Monocyte %, Lymphocyte %, Basophil %, Eosinophil %

^10^Blood Chemistry Panel: BUN, Creatinine, EGFR, NA, K, GLU, Cl, CO_2_, TP, ALB, ALKP, AST (SGOT), ALT (SGPT), LDH, CPK, TBIL, DBIL

^11^Coagulation Panel: PT, INR, APTT, Fibrinogen

^12^In the outpatient setting if the subject is not seen by study staff for any other reason, surveillance calls are to be completed at least monthly (at minimum every 35 days) to collect AEs, SAEs, TRs, and UADEs starting from the initiation of the first study transfusion through the entire transfusion support period and through 28 days after the final study transfusion. If the monthly surveillance call interval coincides with a study visit, data will be collected at the study visit

**Table 2 Tab2:** Schedule of Enrollment, Interventions, and Assessments: 28-Day Plus 6-Month Extension for Sickle Cell Disease Patients Undergoing Red Cell Exchange (RCE) Patient population: Sickle Cell Disease patients on a regular, repeated RCE program receiving 3 consecutive RCE procedures. Note: Pre-allocation screening and randomization steps are the same as those in Table 1. The footnote numbering scheme in this table also maps to Table 1

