### Transfusion support periods: 28-day acute transfusion support or 28-day + 6-month extension

Subjects will receive amustaline/GSH (Test) or conventional (Control) RBCs during the transfusion support period into which they have been enrolled, or until death, whichever is first. The day of the first study transfusion will be considered study Day 1 for defining the transfusion support period. Transfusions will be administered according to local institutional policy and safety standards as ordered by the medical team.

Data on all AEs, serious AEs (SAEs), transfusion reactions (TRs) and/or Unanticipated Adverse Device Effects (UADEs) will be collected from the initiation of the first study RBC transfusion through 28 days after the last study RBC transfusion. SAEs are required to be reported by the Investigator to the Sponsor or designee immediately (i.e., no more than 24 h after learning of the event). In an inpatient setting bleeding status and safety events will be collected daily following each study RBC transfusion until discharge or death, whichever is first. In the outpatient setting surveillance calls are to be completed at least monthly (at minimum every 35 days) if the subject is not seen by study staff for any other reason. If the monthly surveillance call interval coincides with a study visit, these data may be collected as part of the study visit assessments described in Tables 1 and 2.

For pediatric patients, the volume of the intended transfusion should be recorded. Study staff will record the proportion of the transfused unit. If for any reason a unit is not fully transfused, the percentage of the bag that was transfused (i.e., 75%, 50%, 25%) and the reason the remainder of the unit was not transfused or the why the transfusion was stopped will be recorded. This proportion will be recorded for each unit of study RBCs transfused and combined with the Hb concentration and net volume of the RBC component as measured by the blood center. These variables will be used to calculate the actual Hb mass transfused.

A negative antibody screen for amustaline/GSH RBCs should be confirmed prior to transfusing a patient with study RBCs and each time a standard of care ABO Type, Rh and screen (IAT) test is performed within the 28-day acute transfusion period and the 6-month extension period, if applicable.

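### For deaths, the Hb-consumption denominator has no cap at the planned end of the transfusion period, so a death in follow-up can lengthen it

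*Protocol article*

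**What the plan says.** Adjusted Hb consumption is a secondary efficacy endpoint: total Hb mass transfused, divided by baseline weight and by the duration of the study transfusion period. Statistical methods gives the length of that period as "i.e., 28 days or 28-day + 6-months, unless subjects prematurely discontinue the study". The analysis is a formal non-inferiority test (Test – 1.15 × Control), limited to non-bleeding mITT subjects who take part in both the 28-day and the 6-month extension periods.

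The exception has its own rule: "For patients who prematurely discontinue from the study, the duration of the study transfusion period will be calculated as" end date minus start date plus 1. The end date then depends on the reason for leaving:

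- Death: "For subjects who withdraw due to death, the date of death will be the end date of the study transfusion period".
- Any other reason: "the last date of a study or non-study RBC transfusion during the planned study transfusion period (28-days or 28-day + 6-months".

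Three other places bear on this:

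- The 28-day follow-up section: "The last study transfusion will occur no later than the end of the 28-day acute transfusion period or the 6-month extension period".
- Table 1, footnote 5: "The date of non-study RBC transfusion, if any, during the 28-day follow-up period and 6-month extension, if applicable, must be documented".
- The Day 75 (± 15 days) visit, counted from the last study transfusion, is the end of study. Table 1 has vital status recorded there, but no transfusion data.

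**The concern.** The formula is triggered by leaving the study, but the quantity it computes is the length of the transfusion period. The study continues for about 75 days after the last study transfusion, so a subject can complete the transfusion period and still meet the trigger by dying in follow-up. For that subject the death rule puts the end of the transfusion period after its planned end. The non-death rule beside it carries the limit that the death rule lacks.

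The added days do not belong in the ratio. No study RBC can be given in them, and after the 28-day follow-up the article requires no record of non-study RBCs. The denominator of a formally tested endpoint would then depend partly on survival after treatment.

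The same trigger also affects survivors. A subject who completes the period and is then lost before Day 75 is cut back to the date of the last transfusion, which shortens the denominator.

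**Working it through.** The article states no sample size, event rate or variance for Hb consumption, so there is no figure of the plan's own to reproduce here. The stated sizing is for the Hb increment and does not enter.

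**Inputs**
- Planned period for this analysis set: 28 days + 6 months (Statistical methods). The article does not convert 6 months to days. Taking 183 days, L = 28 + 183 = 211 (assumption).
- x = days from the planned end to death. Day 75 ± 15 is counted from the last study transfusion, so x reaches 75 or 90 only if that transfusion falls on the last planned day.
- Share of an arm that completes the period and dies in follow-up: not given. 5% and 10% are assumed.

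**One subject, no Hb added.** The uncapped value is L/(L + x) of the capped value.

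| x (days) | Denominator (days) | Ratio | Fall in g/kg/day |
|---|---|---|---|
| 28 | 239 | 211/239 = 0.883 | 11.7% |
| 75 | 286 | 211/286 = 0.738 | 26.2% |
| 90 | 301 | 211/301 = 0.701 | 29.9% |

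**Offset from captured non-study RBCs.** The numerator covers the same period, so non-study RBCs recorded in the first 28 follow-up days would count. Let H be the Hb mass in the planned period and h the mass added. The value is unchanged when h/x = H/L. At x = 28 this means h = 28/211 = 13.3% of H. Less than that leaves a net fall, and more gives a rise, so the direction is uncertain for deaths in the first 28 days. If transfusion continues at the earlier rate for 28 days and nothing is recorded afterwards, the fall is 1 – 239/286 = 16.4% at x = 75 and 1 – 239/301 = 20.6% at x = 90. The 26.2% and 29.9% are therefore upper values.

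**Earlier last study transfusion.** Study transfusion may stop at the tenth episode, before the planned end.
- Last on day 100, death 75 or 90 days later: day 175 or 190, inside 211 days. A cap changes nothing.
- Last on day 150, death 75 days later: day 225; 1 – 211/225 = 6.2%.
- Last on day 190, death 75 days later: day 265; 1 – 211/265 = 20.4%.

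**Arm mean, no Hb added.** Shift = share × individual fall, if affected subjects otherwise have average consumption.
- 5%: 0.05 × 11.7% = 0.6% (x = 28) to 0.05 × 29.9% = 1.5% (x = 90).
- 10%: 1.2% to 3.0%.

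For scale, the extension target of 140 includes up to 30 red cell exchange subjects, who are classed as bleeding and so fall outside this analysis. That leaves about 110, or 55 per arm, and 5% of 55 is about 3 subjects.

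**Loss to follow-up after completing the period.** With a last transfusion on day 190 (illustration), the denominator is 190 instead of 211, and the value rises by 211/190 – 1 = 11%.

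**The case against.** The strongest reply is that the article already bounds the period. The rule defines the end of the transfusion period, not of the study. The section on transfusion support periods says that subjects receive study or control RBCs "during the transfusion support period into which they have been enrolled, or until death, whichever is first". Follow-up is a separate, named period. On this view death can shorten the period but cannot reopen one already completed.

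This shows that a cap was probably intended, but it does not supply one. The support-period sentence governs how long subjects receive RBCs, not the denominator. The definition in Statistical methods exempts subjects who discontinue the study early, which sends them to the uncapped rule. What stands is that this is a conflict between passages and not a settled intention to count follow-up days. The SAP is not shown and may already resolve it.

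The objections on size also stand. A reader might infer that 28-day subjects are hit hardest, since a fixed number of extra days weighs more on a 28-day denominator. The documents do not support this, because the analysis is restricted to extension participants. A reader might also infer that no transfusions are captured in follow-up, or that the rule uniformly understates consumption. Neither follows: non-study transfusion dates are required through the 28-day follow-up, and those units enter the numerator.

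Finally, a cap does not remove planned days without study transfusion after an early tenth episode. That is a separate feature of the endpoint.

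**Conclusion.** The point holds as a minor one. Read literally, the death rule contradicts the period defined in the same section, because it can extend the denominator into follow-up while the adjacent rule cannot. For an extension subject with a last study transfusion at the end of a 211-day period (6 months taken as 183 days), death 75 or 90 days later lowers the value by up to 26% or 30%. The effect is smaller or absent when study transfusion ended earlier, and of uncertain direction for deaths within the first 28 follow-up days.

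At an assumed 5% of an arm, the mean moves by about 0.6% to 1.5%, against a margin of 15% on a secondary endpoint. It would be tempting to conclude that the rule favours the Test arm. The documents give no follow-up death rates, and similar deaths in both arms would scale both means alike. The comparison is biased only if such deaths differ between arms.

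**What to change.** For deaths, define the end date as the earlier of the date of death and the planned end of the study transfusion period. Apply the duration formula only to subjects who discontinue before that planned end. All others, including those who die or are lost during the 28-day or 75-day follow-up, keep the full planned duration. State the planned end in days, so that 6 months has one meaning.

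This takes a clause or two in the derivation and needs no new data. It restores the period that Statistical methods already defines and corrects the loss-to-follow-up case as well. The Discussion says the study is still blinded, and the article expects the last assessments in the third quarter of 2026, so the wording can be settled before unblinding. If the SAP already says this, the sponsor need only confirm it.
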